### Sample size

A total of 180 adult men (18 years and over) on remand will be recruited from two sites: one within the Scottish Prison Service (SPS) (n=90); and the second from Her Majesty’s Prison and Probation Service (HMPS) in England (n=90). These sites were purposively selected following PRISM-A, as they offer geographical, socioeconomic and ethnic diversity, along with differing procedures and structures.^16^ Both prisons provide alcohol services via external agencies who engage with people in custody and following release. Prisons have varying induction procedures, communication mechanisms and processes, and available, secure space to engage participants. Understanding the different approaches and dynamics will be important when designing a future RCT.

The target population is men on remand in prison, who have been in prison for 3 months or less. The average time on remand is approximately 9 weeks in England^22^ and 4 weeks in Scotland.^23^ We estimate that approximately 50% of participants will be released, while the rest will remain incarcerated; leaving 45 participants per study arm (90 in total) across the two sites.

This sample size was calculated to take account of the following factors^24^:

It will enable calculations of two-sided 95% CIs around proportions recruited, released and dropout in each study arm with half-widths of less than 0.15.It exceeds the 30 per group recommendation of Lancaster *et al*^25^ and 35 participants per group recommendation of Teare *et al*^26^ for estimating key unknown design parameters, for example, SD with sufficient precision with a continuous primary outcome.It will ensure that within each arm, across each site, we satisfy the minimum 12 per group ‘rule of thumb’ outlined by Julious^27^ for pilot trials.

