### Staff training

Two members of VSO staff at each site will be trained to deliver the ABI to participants (intervention), and the remaining staff will have no training (control). This method seeks to minimise contamination and has been used in other similar studies.^30 31^ The possibility of residual contamination and the practicality of allocating staff according to randomisation will be explored within the process evaluation to inform the future RCT. Weekly debriefs with interventionists delivering the APPRAISE ABI will also enable the exploration of possible contamination.

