### Data collection

#### Baseline assessment

Following appropriate consent procedures, baseline (TP0) data will be collected via researcher-led completion of questionnaires, and this will take approximately 30 min. Immediately after, participants will be randomised to the control or intervention arm and informed of their allocation. Participants randomised to the intervention arm will be provided with a face-to-face appointment to meet with their interventionist. This is the process used by the current providers ((VSO)when engaging with individuals in the prison setting. The three telephone sessions will be delivered following release from prison by one of the trained interventionists. In addition to the outcome measures (described below), data on age, gender, marital status, educational status and contact details will be collected.

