#### Blinding

Due to restrictions regarding electronic equipment and mobile phone use by researchers while in prison, a randomisation system, such as an interactive voice response telephone system or one accessed over the web, cannot be used. Allocation will be conducted at participant level using random permuted blocks of variable size^3 5 6^ stratified by site using sealed envelopes, based on a predetermined random number allocation carried out by Edinburgh Clinical Trials Unit (ECTU).^27 35^

Researchers will not be involved in delivering the active and control interventions but will be aware of the study allocation of participants as the trial progresses. Allocation concealment will be used whereby neither the person delivering the interventions nor the participant will be aware of the study allocation until they are irrevocably entered into the trial. Both the trial statistician (RP) and health economist (JB) will be blinded to group allocation and will only have details of study participants by study number.

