### Data analysis

The progress of participants through the APPRAISE pilot trial will be presented in accordance with the CONSORT (Consolidated Standards of Reporting Trials) guidelines^43^ to allow descriptions of key parameters required for a future RCT; eligibility rates, consent, adherence, retention at follow-up and data completeness of outcome measures.

The statistical analyses will be primarily descriptive, providing an estimate of the proportion of those eligible, consenting, adhering to the intervention and retention rates at 6 and 12 months. These parameters will inform the power calculations for a future RCT and confirm or identify the need for modifications in relation to other aspects of the trial design, particularly the acceptability of study processes and outcome measures to participants and staff. Data about the flow of participants through the APPRAISE pilot trial will include numbers screened, the prevalence of the target condition, numbers providing contact details, numbers eligible and willing to consent and numbers followed up successfully at TP1 and TP2. In addition, data completeness for each of the instruments and any potential bias in the follow-up data will be ascertained.

Analysis of the primary outcome will also provide estimates of the variance within and between groups for exploration of sample size calculations for a definitive RCT. Furthermore, we will calculate the variance of all primary and secondary outcome measures within groups to explore their utility in a definitive study. If access to PNC data is possible, proven reconviction rates will be measured by the number of offences committed by each treated participant against the number committed in the comparison group. Time-to-event analysis will also explore differences in offending patterns.

Calculation of between trial-arm differences (with 95% CIs) will indicate the likely effect sizes that will be observed in a future definitive trial.

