For the primary outcome analysis, the mean difference (with 95% CI) in alcohol units consumed between the two randomisation groups will be calculated, both overall and stratified by site. A complete case analysis will be used, but a sensitivity analysis will also be incorporated to explore the effects of missing data. This will involve using multiple imputations for the primary outcome in a supplementary analysis, provided that the valid sample size is sufficient to support this. In addition, we will add and subtract one-unit difference (alcohol units) to the missing data as part of a sensitivity analysis to explore how the 95% CIs change depending on our assumptions about the missing data (bearing in mind that the imputed data cannot be less than zero). This is similar to the sensitivity analysis method suggested in White *et al* (2011) which involves determining how large an amount can ‘*be added to or subtracted from the imputed data without changing the clinical interpretation of the trial’*. We will adopt a similar approach to determine how sensitive the conclusions of the APPRAISE pilot trial (and the decision about whether to proceed with an RCT) are to our assumptions about missing data.

A statistical analysis plan will be written and finalised prior to analysis.

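### Intervention men are nested in a handful of trained staff, but neither the planned arm contrast nor the RCT design parameters allow for it

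*Protocol article*

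**What the plan says.** Under Blinding, the protocol article makes the man the unit of allocation: "Allocation will be conducted at participant level using random permuted blocks of variable size", stratified by site. Staff training limits who delivers the intervention: "Two members of VSO staff at each site will be trained to deliver the ABI to participants (intervention"). The remaining staff are untrained and serve the control side. Under Baseline assessment, each intervention man is given an appointment with his interventionist, and "The three telephone sessions will be delivered following release from prison by one of the trained interventionists".

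For the primary outcome, Data analysis states that "the mean difference (with 95% CI) in alcohol units consumed between the two randomisation groups will be calculated, both overall and stratified by site". It adds, in a sentence that ends by naming the RCT: "Analysis of the primary outcome will also provide estimates of the variance within and between groups for exploration of sample size calculations for a definitive". The arm differences with their intervals are also meant to show what effect sizes a definitive trial is likely to see. Objective 1b names the standard deviation and the recruitment, retention and follow-up rates as design parameters. Neither place mentions variation between interventionists. Shared staff are discussed only as a possible source of contamination.

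Mechanisms of impact refers to interviews with eight intervention staff, whereas Staff training implies four trained deliverers.

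**The concern.** A talking intervention given by a few people can work better in some hands than in others. The article itself plans to record and code a fifth of sessions for quality. Men seen by the same interventionist may then have correlated outcomes, while control men have no matching trial-delivered grouping. This is a partially nested design.

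Stratifying by site does not deal with it, because two interventionists work within each site. The extra variance matters in two places: the width of the interval around the arm difference, and the size of an RCT planned from this pilot, which is the pilot's stated purpose.

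**Working it through.** **Inputs from the protocol article.** 180 men (Sample size). Equal arms, implied by "leaving 45 participants per study arm (90 in total) across the two sites", so 90 per arm at entry. Four trained interventionists (Staff training). Follow-up target 60% at 12 months and uptake target 70% receiving at least one session (Objective 4). The article gives no ICC, so 0.01 to 0.10 is assumed here.

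**The plan's own precision figure.** Half-width below 0.15 for a proportion in each arm: 1.96 × √(0.25/45) = 0.146. This reproduces. It concerns proportions, not the mean difference.

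**Caseload m.** At entry 90/4 = 22.5. At 60% follow-up, 54 per arm and 54/4 = 13.5. Within one site, 45 intervention men over two staff again gives 22.5, so the site-specific intervals are affected by the same ratio.

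**Standard error.** Design effect in the intervention arm DE = 1 + (m − 1) × ICC; control arm 1. Ratio of correct to plain standard error = √((DE + 1)/2). Coverage is that of the plain 95% interval, simulated with four interventionists, 20,000 runs and whole-number caseloads.

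| Analysed per arm | ICC | DE | SE ratio | Half-width, SD units (plain → correct) | Coverage |
|---|---|---|---|---|---|
| 54 | 0.01 | 1.125 | 1.03 | 0.377 → 0.389 | 0.95 |
| 54 | 0.02 | 1.250 | 1.06 | 0.377 → 0.400 | 0.93 |
| 54 | 0.05 | 1.625 | 1.15 | 0.377 → 0.432 | 0.91 |
| 54 | 0.10 | 2.250 | 1.28 | 0.377 → 0.481 | 0.88 |
| 90 | 0.01 | 1.215 | 1.05 | 0.292 → 0.307 | 0.94 |
| 90 | 0.02 | 1.430 | 1.10 | 0.292 → 0.322 | 0.93 |
| 90 | 0.05 | 2.075 | 1.24 | 0.292 → 0.362 | 0.89 |
| 90 | 0.10 | 3.150 | 1.44 | 0.292 → 0.421 | 0.83 |

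A ratio of 1.24 means the plain standard error is 1 − 1/1.24 = 19% too small.

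**What shrinks it.** With 54 per arm and 70% uptake, 37.8 men are treated, 9.45 per interventionist. DE = 1 + 0.7 × 8.45 × 0.05 = 1.296 and the ratio is √(2.296/2) = 1.07 at ICC 0.05. With eight deliverers, 54 per arm and full uptake, m = 6.75, DE = 1 + 5.75 × 0.05 = 1.2875 and the ratio is again 1.07.

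**Are the pilot variances biased?** The expected intervention-arm sample variance, relative to the true total variance, is 1 − ICC × (m − 1)/(n − 1). At ICC 0.10 and n = 54 this is 1 − 0.10 × 12.5/53 = 0.976; at ICC 0.01 it is 0.998. Hardly.

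**RCT size.** The inflation is (DE + 1)/2. At ICC 0.02 it is 1.125 (m = 13.5) or 1.215 (m = 22.5). At ICC 0.05 it is 1.31 or 1.54. As an illustration, assume a standardised difference of 0.3 and 90% power: 234 per arm unadjusted. With m = 13.5, 264 are needed at ICC 0.02 and 308 at ICC 0.05. Staying at 234 gives about 86% and 81% power.

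**The case against.** The strongest reply is that this is analysis-plan detail. The article names a contrast, not a model or a standard error, calls the analyses mainly descriptive, and promises a statistical analysis plan. A clustered standard error is compatible with the same mean difference. That stands as far as it goes: a reader might infer that the men will be treated as independent, but the article never says so. What remains is that the article does set out the contrast, its only stratifier, the missing-data analyses and the parameters wanted for the RCT, and interventionist variation appears in none of them.

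A reader might also infer that the pilot variances are defective and that the RCT will therefore be too small. The documents do not support this. The variances are nearly unbiased, no RCT calculation is fixed, and the parameter list in Objective 1b is not presented as exhaustive.

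Nor can it be concluded that the interventionist goes unrecorded. Intervention delivery summarises dose items rather than listing fields, and each man has a designated interventionist.

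The nesting is not clean. Telephone sessions may come from a different trained person, about half the men are expected to stay incarcerated while three of the four sessions follow release, and control men may also see voluntary-sector staff. The operational progression criteria do not use this interval.

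Finally, an interval need not generalise beyond the four staff. But the article wants the arm differences to indicate effects in a definitive trial, which would need other staff too.

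**Conclusion.** The concern holds in a conditional and moderate form. As written, the primary contrast and the RCT parameters leave out between-interventionist variance, which stratifying by site cannot remove. If the ICC is above zero, an ordinary 95% interval is too narrow. At the 60% follow-up target with full uptake, the standard error is understated by a factor of 1.03 to 1.28 (1.15 at ICC 0.05). With every man analysed the factor is 1.05 to 1.44. At ICC 0.01 to 0.02 after losses the effect is only 3% to 6%, and at 70% uptake or with eight deliverers it is smaller than the full-uptake, four-deliverer figures.

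The larger consequence is for the RCT. At similar caseloads, omitting the design effect would leave it short by about 12% to 21% at ICC 0.02, or 31% to 54% at ICC 0.05. These results rest on the assumed ICC range, equal caseloads, clustering in the intervention arm only, and four deliverers.

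**What to change.** 1. Make sure that the interventionist assigned for the face-to-face session is kept as an analysis variable.
2. Keep the planned mean difference. Add a sensitivity 95% interval with variance s₁²[1 + (m − 1)ICC]/n₁ + s₀²/n₀ over a fixed ICC range, for example 0.01 to 0.10, stated as an assumption.
3. State in Data analysis that the RCT sample-size exploration will apply a partially nested design effect over that range. Do not use the pilot's own ICC: with four interventionists, 54 men and a true value of 0.05, 95% of simulated estimates fell between about −0.07 and 0.26. For the same reason, do not rely on a mixed model fitted to the pilot.
4. Reconcile the eight intervention staff under Mechanisms of impact with the four trained staff under Staff training, since the caseload depends on it.

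The cost is one retained variable and a few lines of analysis. The sensitivity interval will be somewhat wider and the projected RCT larger. The pilot needs no extra participants, staff or procedures.

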#### Follow-up

Follow-up assessments will be conducted at 6 (TP1) and 12 months (TP2) post recruitment. The original aim was for these to be conducted by the researcher either in person or by telephone. In light of COVID-19 restrictions, follow-up assessments have also been adapted to enable self-completion using hard copies or electronic versions. Where participants are identified as being incarcerated at follow-up, arrangements with the relevant prison will be made to undertake the follow-up. Attempts to contact participants will be multifaceted, including telephone calls, text messages and emails, based on participants’ preferred method of contact, at varying times and days of the week. We will record the number of participants invited to participate; responded; were eligible; recruited; transferred; subsequently sentenced; liberated, and lost to follow-up. The number who returned to prison during the 12 months and who completed the trial will also be recorded.

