### Outcomes

#### Primary outcome measure

The proposed primary outcome measure is alcohol consumed, in units where one unit equals 8 g or 10 mL of ethanol, per week will be derived from the frequency and quantity of alcohol consumption questions in the extended version of AUDIT using a formula developed and employed in a number of RCTs of interventions for alcohol consumption.^36 37^ A score of 8+ is referred to as a ‘positive screen’ and indicates drinking at hazardous (score of 8–15), harmful (score of 16–19) or probable dependent level (score of 20+). A score of 8 or more out of a possible 40 on the AUDIT has an established sensitivity of 92% and specificity of 94%^28^ to detect those at risk of harm from alcohol use. The AUDIT will be administered at TP0, TP1 and TP2.

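### The overall primary arm difference is planned as a raw complete-case mean difference, although baseline units and the randomisation stratum (site) are available to adjust for

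*Protocol article*

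**What the plan says.** All references are to the protocol article.

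- **Effect measure (Data analysis).** For the primary outcome, "the mean difference (with 95% CI) in alcohol units consumed between the two randomisation groups will be calculated, both overall and stratified by site". No covariate is named.
- **Analysis set (Data analysis).** "A complete case analysis will be used, but a sensitivity analysis will also be incorporated to explore the effects of missing data". The sensitivity work is "multiple imputations for the primary outcome in a supplementary analysis, provided that the valid sample size is sufficient to support this", plus a shift of one alcohol unit up and down in the missing values.
- **When the outcome is measured (Primary outcome measure; Follow-up).** Weekly units are derived from the extended AUDIT, and "The AUDIT will be administered at TP0, TP1 and TP2". TP0 is baseline; TP1 and TP2 are 6 and 12 months after recruitment.
- **Randomisation (Blinding).** Permuted blocks, "stratified by site using sealed envelopes".
- **Use of the result (Data analysis).** The analyses are mainly descriptive. The arm differences with their CIs are nevertheless to guide expectations of effect size for a definitive trial, and variances are to feed its sample size. Objective 1b asks for the parameters needed for that calculation and gives an open list that includes the SD.
- **Still to come.** A statistical analysis plan is to be written before analysis; it is not shown.

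**The concern.** The article fixes a method here, so this is more than a detail left open. An analysis plan that followed the wording would carry forward a raw difference in means as the main overall result.

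Two pieces of information already in hand would then go unused. Baseline units on the same instrument can explain part of the between-man variation in follow-up drinking and correct for chance imbalance between arms. Site was used to stratify the allocation, and an overall analysis that ignores a stratification factor tends to give an interval slightly wider than it need be. Separate differences for each site do not supply an adjusted overall estimate.

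At stake is the width of the interval around the estimate that the definitive trial's designers will look at. So is the choice of SD for the next sample size: the raw SD alone, or also the smaller residual SD if the correlation is appreciable.

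**Working it through.** **1. The article's own precision figure.** The Sample size section plans 180 men, "leaving 45 participants per study arm (90 in total) across the two sites" after about half are released, and claims a 95% CI half-width below 0.15 for a proportion in each arm. At p = 0.5 and n = 45: 1.96 × √(0.25/45) = 0.146. The figure reproduces and is not affected by this point. The article gives no SD, effect size or correlation for units, so the results below are in SD units and the correlation ρ is an assumption shown as a range.

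**2. Effect of baseline adjustment on the CI.** For n men per arm:

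- Unadjusted half-width = t(0.975; 2n − 2) × √(2/n).
- Adjusted half-width = t(0.975; 2n − 3) × √[(2/n)(1 − ρ²)(1 + 1/(2n − 4))]. The last factor is the small price of chance baseline imbalance.

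Three values of n are used: 54 (60% of 180 = 108, over two arms), 45 (the article's figure) and 27 (60% of 90 = 54, over two arms). The 60% is the 12-month progression threshold in Objective 4d, borrowed only as a scenario.

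| n per arm | unadjusted | ρ = 0 | ρ = 0.1 | ρ = 0.3 | ρ = 0.5 | ρ = 0.7 |
|---|---|---|---|---|---|---|
| 54 | 0.382 | 0.383 | 0.382 | 0.366 | 0.332 | 0.274 |
| 45 | 0.419 | 0.421 | 0.419 | 0.402 | 0.365 | 0.301 |
| 27 | 0.546 | 0.552 | 0.549 | 0.526 | 0.478 | 0.394 |

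At n = 54 the ratios to the unadjusted width are 0.959, 0.870 and 0.718 for ρ = 0.3, 0.5 and 0.7, so the interval is about 4%, 13% or 28% narrower. At ρ = 0.1 or less the ratio lies between 1.000 and 1.010 across the three sizes: no gain, and at most 1% lost.

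**3. Site alone.** With two equal sites that differ by d SD, R² = 0.25d²/(1 + 0.25d²) and the SE is multiplied by √(1 − R²). For assumed d = 0.2, 0.3 and 0.5, the factors are 0.995, 0.989 and 0.970, a fall of 0.5%, 1.1% and 3.0%.

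**4. Using the 6-month value, if the comparison is at 12 months.** Let a fraction 0.6 have TP2 and a further fraction e have TP1 only. Under missing at random, the variance factor is 0.6 × [ρ₁₂²/(0.6 + e) + (1 − ρ₁₂²)/0.6], where ρ₁₂ is the TP1 to TP2 correlation. With e = 0.05 and ρ₁₂ = 0.5 it is 0.981 (SE factor 0.990). With e = 0.20 and ρ₁₂ = 0.7 it is 0.877 (SE factor 0.937). The gain is about 1% to 6% of the SE; all these inputs are assumed.

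**5. Why the correlation is worth reporting.** As an illustration only, take a standardised effect of 0.3, 90% power and a two-sided 5% level. The unadjusted size is 2 × [(1.960 + 1.282)/0.3]², or 234 per arm. Multiplied by 1 − ρ², it becomes 213, 176 or 120 at ρ = 0.3, 0.5 or 0.7. The pilot would estimate ρ only roughly. By Fisher's z, an observed 0.5 has a 95% CI of 0.34 to 0.63 with 108 completers and 0.27 to 0.68 with 54.

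**The case against.** The strongest reply is that this is a descriptive pilot with no power claim, that its progression criteria (Objective 4) do not use the arm difference, and that a condensed article may leave covariates to the analysis plan. Low correlation is also plausible. Men may have been in custody for up to three months at entry, about half are expected to stay incarcerated, and some follow-ups will take place in prison. Sizing the next trial on the raw SD would err on the safe side. All of this limits the consequence. It does not answer the point that the stated method is raw, that the estimate has a declared use, and that adjustment costs almost nothing even when it gains nothing.

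Several stronger readings are tempting but not supported:

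- **That the correlation and residual SD will not be estimated.** They are not listed, but Objective 1b's list is open, the data are collected and the analysis plan is not shown. Nor does the article say how the definitive trial would be analysed.
- **That site is ignored.** Results by site are planned; only a site-adjusted overall estimate is absent.
- **That complete-case analysis discards every man seen at only one follow-up.** A man seen at the analysed visit is kept. In a 12-month comparison only those seen at 6 months alone drop out, and the primary-outcome paragraph of the Data analysis section does not say which visit is analysed.
- **That the raw difference is unbiased only if data are missing completely at random.** Missingness that depends on arm alone, or bias that is equal in both arms, leaves the difference intact.
- **That 40% loss is expected.** The 60% is a progression threshold, not a forecast.
- **That missing data are left unaddressed.** Conditional multiple imputation and the one-unit shift are planned, and the imputation could use TP0 and TP1.

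**Conclusion.** The point holds in a limited form. As written, the overall primary comparison is an unadjusted complete-case mean difference, although baseline units and the stratification factor are at hand. An estimate adjusted for both is a near-free improvement. No figure in the article becomes wrong, and the raw difference is not invalid.

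Baseline is the main lever, and its value rests wholly on an assumed correlation: about 4%, 13% or 28% off the CI width at 0.3, 0.5 or 0.7, and nothing at 0.1 or below. Site and the 6-month value each add only a few percent, again under assumptions. A reader might infer that a repeated-measures model is needed; the documents do not support that. Such a model rests on missing at random, which is also untestable, and its benefit depends on a 12-month analysis that is not stated.

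**What to change.** In the statistical analysis plan:

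1. Make the main overall estimate the mean difference in weekly units with 95% CI from an ANCOVA, with TP0 units and site as covariates.
2. Keep the raw difference beside it, and keep the site-specific differences.
3. Report the residual SD and the baseline to follow-up correlation with its 95% CI, labelled as inputs to the definitive trial's sample size, alongside the raw SD.
4. State which visit the main comparison uses. If it is 12 months, a repeated-measures model on TP1 and TP2 may be added as an optional supplement to retain men seen only at 6 months.

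The cost is a few sentences of wording and one model. No extra data or participants are needed.

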#### Objective 4: to assess whether operational progression criteria for conducting a future definitive RCT are met across trial arms and study sites and if so, develop a protocol for an RCT. *Operational progression criterion are based on previous research results*^3^

4a. Do the two prisons invited to the study agree to take part?

4b. Based on knowledge from previous data, do at least 90 eligible participants consent to take part and be randomised?

4c. Do at least 70% of participants allocated to the intervention condition go on to receive at least one intervention session?

4d. Do at least 60% of participants take part in the follow-up assessments at 12 months across trial arms and study sites?

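### The only stated departure from missing-at-random is a shift of one alcohol unit a week, too small to test robustness and not the search for a tipping point that the protocol invokes

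*Protocol article*

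**What the plan says.** The proposed primary outcome is "alcohol consumed, in units where one unit equals 8 g or 10 mL of ethanol, per week" (Primary outcome measure). For its analysis, "the mean difference (with 95% CI) in alcohol units consumed between the two randomisation groups will be calculated, both overall and stratified by site" (Data analysis).

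The Data analysis section gives three layers for missing data:

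- The main analysis: "A complete case analysis will be used, but a sensitivity analysis will also be incorporated to explore the effects of missing data".
- A supplementary analysis: "using multiple imputations for the primary outcome in a supplementary analysis, provided that the valid sample size is sufficient to support this".
- A further step: "we will add and subtract one-unit difference (alcohol units) to the missing data as part of a sensitivity analysis". The aim is to see how the 95% CIs move, with imputed values not allowed below zero.

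The section describes the third step as similar to a published approach that asks how much can be added to or taken from imputed values before the clinical reading of the trial changes. It says the step will show how sensitive the conclusions are, and also "the decision about whether to proceed with an RCT". It names no amount other than one unit, and it does not say whether one arm or both are shifted.

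Objective 4 sets the retention criterion 4d: "Do at least 60% of participants take part in the follow-up assessments at 12 months". The criterion can therefore be met with up to 40% of outcomes missing.

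**The concern.** In the method that the protocol cites, the size of the shift is the result: the analyst keeps increasing it until the reading changes, then judges whether a shift that large is credible. Here the size is fixed in advance at one unit, so the question of how large is never asked.

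One unit a week also looks very small for men who enter with an AUDIT score of 8 or more, a range that runs up to probable dependence. Missingness could plausibly depend on drinking. Men still in prison can be reached through the prison, while released men must be traced by phone, text or email (Follow-up), and the Introduction notes that alcohol is more widely available after release. That link is an inference; the protocol gives no data on it.

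The arm differences are meant to indicate likely effect sizes for the definitive trial. A check that moves them very little would make them look sturdier than has been shown.

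**Working it through.** **Inputs**

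- Shift d = 1 unit a week (Data analysis).
- 180 randomised (Sample size). Taking 1:1 allocation, which the stated 45 per arm after release implies, gives 90 per arm.
- Missing share m = 0.40, the most that meets criterion 4d. Observed per arm: 90 × 0.60 = 54.
- SD of weekly units: not given, since the pilot is to estimate it (Objective 1b). Assumed 20 to 60, with 10 as a low extreme.

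**The plan's own precision figure.** The protocol gives no figure for the effect of the shift. The nearest is a half-width below 0.15 for proportions in each arm. With 45 per arm and p = 0.5, 1.96 × √(0.25/45) = 0.146, so that figure is reproduced.

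**Movement of the arm difference.** Shifting a share m of an arm's values by d moves that arm's mean by m × d.

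- One arm shifted: 0.40 × 1 = 0.4 units a week.
- Arms shifted in opposite directions: 2 × 0.40 × 1 = 0.8.
- Both shifted the same way: (m₁ − m₂) × 1, which is 0 with equal missingness and 0.2 with 50% against 30%.

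The floor at zero hardly matters. A simulation of the opposite-direction case, with skewed (gamma) outcomes and mean and SD both 30 or both 50, gave 0.79 to 0.80.

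**Comparison with the CI.** Complete-case half-width = 1.96 × SD × √(2/54) = 0.377 × SD.

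| Assumed SD | Half-width | 0.4 as share | 0.8 as share |
|---|---|---|---|
| 10 | 3.8 | 10.6% | 21.2% |
| 20 | 7.5 | 5.3% | 10.6% |
| 40 | 15.1 | 2.7% | 5.3% |
| 60 | 22.6 | 1.8% | 3.5% |

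Using t with 106 degrees of freedom gives 7.6, 15.3 and 22.9 for SD 20, 40 and 60, which changes nothing of substance.

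With 45 per arm, which is also the size of each arm within one site (90/2), 27 are observed. The half-width at SD 20 is then 10.7, and the shares fall to 3.7% and 7.5%.

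**Shift needed to move the difference by one half-width at 40% missing (54 observed per arm).** One arm: 0.377 × SD / 0.4 = 0.94 SD. Opposite directions: 0.377 × SD / 0.8 = 0.47 SD. In units:

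- SD 10: 9.4 or 4.7
- SD 20: 18.9 or 9.4
- SD 50: 47.1 or 23.6

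All are several times to many times the one unit stated.

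**The case against.** The strongest reply is that one unit may be only a step or an example. The protocol states the tipping-point aim, says a similar approach will be adopted, and defers to a statistical analysis plan that is not shown; the grid, the arms and the stopping point are normal content for such a plan. This reading is possible, but the article does not state it. It commits to one specific amount and gives that amount a purpose, so the point is about what is written and not about missing detail.

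Three stronger readings are tempting, and the document does not support them:

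- A reader might infer that the plan cannot reveal any dependence on missing data. It can reveal some: multiple imputation may differ from complete cases, and the Data analysis section also promises to look for bias in the follow-up data. A CI limit lying very near a boundary could also cross it under a one-unit shift. But standard imputation assumes missing at random and is planned only if the sample allows, so the one-unit shift remains the only stated departure from that assumption.
- A reader might infer that the movement is always below one unit. For opposite shifts it reaches 1.0 at 50% missing and 1.2 at 60%. Forty per cent is what criterion 4d tolerates, not a forecast or a cap.
- A reader might infer that the link to the decision to proceed should be deleted, since criteria 4a to 4d do not use the drinking outcome. Those are operational criteria. Under Monitoring, the Trial Steering Committee independently assesses the data analysis and determines whether a future trial is merited, so the outcome can matter by that route.

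It also stands that the SD is assumed, that the protocol gives no minimally important difference, and that the analysis is mainly descriptive.

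**Conclusion.** The point holds for the one-unit step. At 60% follow-up it moves the arm difference by 0.4 or 0.8 units a week, or not at all, depending on how it is applied. When non-zero, that is about 2% to 11% of the CI half-width for SD 20 to 60, and at most 21% at SD 10. A shift of that size is too small to test robustness, and fixing it in advance does not carry out the method the protocol cites.

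The figures rest on 1:1 allocation, 40% missing in each arm where arms are compared, and the assumed SDs. The conclusion is not sensitive to the SD: about half an SD in opposite directions, or one SD in one arm, is needed to move the difference by one half-width.

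The consequence is an uninformative supplementary analysis in a pilot without a planned efficacy conclusion. It should be corrected before the analysis plan is finalised, but it does not undermine the trial.

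**What to change.** Replace the single plus-or-minus one unit with a delta-adjusted multiple imputation:

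1. Apply a range of shifts to the imputed values, separately by arm, so that one-arm and opposite-direction cases are both covered.
2. Scale the shifts to the observed SD (for example 0, ±0.25, ±0.5 and ±1 SD) or make them multiplicative (for example ×0.5 to ×2), with a floor at zero.
3. Say beforehand what counts as a changed interpretation of the CI. Extend the range until that happens, and report the tipping point with a comment on whether a shift that large is credible.
4. Keep the reference to the decision to proceed, but state how the outcome result enters it, for example through the steering committee's assessment, since criteria 4a to 4d do not use it.

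The cost is wording in the analysis plan and a few more imputation runs. No further data are needed. If the sample proves too small for imputation, the plan should say that no departure from missing-at-random was tested, and should not rely on the one-unit shift.
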